**4. OBJECTIVE**

**4.1 PRIMARY OBJECTIVE**

- To determine the effects of probiotics (multistrains of Lactobacillus and Bifidobacterium ) on constipation among Parkinson disease patients compared to placebo
- To determine the effects of probiotics on Gastrointestinal Transit Time (GTT) compared to placebo

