|  | **6. HOSPITAL PROFILE/DEMOGRAPHIC**  **7. STUDY PERIOD**  June 2018 – June 2019  **8. SUBJECTS**  **8.1 TARGET POPULATION**  Patients with Parkinson disease attending the neurology outpatients clinic who fulfil inclusion and exclusion criteria  **9. SAMPLING**  **9.1 INCLUSION CRITERIA**   1. Idiopathic PD diagnosed using UK PD Society Brain Bank Criteria 2. Diagnosis of constipation according to Rome III Functional Constipation Criteria 3. Written informed consent   **ROME III Diagnostic Criteria : Functional Constipation**   \| Functional Constipation \| \| --- \| \| Must include 2 or more of the following:  Straining *  Lumpy or hard stools*  Sensation of incomplete evacuation*  Sensation of anorectal obstruction/blockage*  Manual manoeuvres to facilitate defecation(digital evacuation, support of pelvic floor)*  <3 defecation per week*  ***≥25% of defecations**  Loose stool rarely present without use of laxatives  Insufficient criteria for IBS \|   Based on Longstreth GF et al.Gastroenterology 2006 ;130:1480-1491  **9.2 EXCLUSION CRITERIA**   1. Secondary Parkinsonism 2. Previous history of small and large bowel disease 3. Previous extensive gastrointestinal tract surgery 4. Positive stool occult blood in the last 1 month 5. Use of probiotics or antibiotics in 2 weeks before baseline visit 6. Underlying Dementia 7. Hypothyroidism 8. Diagnosed with major depression and on antidepressant 9. Lactose intolerance   10. Type 1 and Type 2 DM  **10. DATA COLLECTION**  **10.1 METHOD OF DATA COLLECTION**  Patients with idiopathic PD attending the neurology outpatients’ clinic will be invited to participate in the study. All subjects will be screen for constipation by using Rome III Criteria – Constipation Module. Written informed consent will be obtained from all subjects after screening inclusion and exclusion criteria. Baseline demographic data will be recorded into a structured questionnaire.  Screening assessment :  1) Constipation screening using Rome III Criteria – Constipation Module  2) Fecal occult blood testing - negative test will be included in the study  The eligible subjects will be assess on the first visit as below :  1) Constipation symptoms by using Garrigues Constipation module (GQ)  2) Quality of life by using PDQ39 Questionnaire (self-administered malay version )  3) Parkinson Disease severity by using MDS-UPDRS  4)Non motor symptoms of PD by using NMS scale  (All the above questionnaires are validated)  Subsequently, subjects will be instructed to consume 4 red carmine capsule(food colourant) and once the stool turn red in colour, Gatrointestinal Transit Time(GTT) will be measured and recorded. Subjects will then receive a 3g sachet of either probiotics (containing multistrains of lactobacillus and Bifidobacterium 30 Colony Forming Unit) or placebo twice-daily for a duration of 8 weeks. Once consumption completed, subjects need to consume again another 4 red carmine capsule and GTT will be measured and recorded again. Final assessment will be done once subjects completed all the probiotics or placebo given(week 8) and subjects need to be assess again on constipation symptoms, non-motor symptoms, quality of life and disease severity same as done at baseline using the same questionnaire.  **10.2 STUDY PROTOCOL**  Randomization  All patients who fulfill inclusion and exclusion criteria will be stratified based on age, sex and background social economics. Patients who are enrolled will be randomized into two treatment groups which a probiotics group who will receive probiotics (containing multistrains of lactobacillus and Bifidobacterium 30 Colony Forming Unit) or placebo using blocks randomization method, in blocks of 4. Patients and investigator will remain blinded to the treatment protocol.  Following randomization, patients will receive their assigned treatment from the pharmacy department, Hospital Canselor Tuanku Muhriz, PPUKM  Treatment  Active treatment group will receive a 3 gram sachet of probiotics containing multistrains of lactobacillus and Bifidobacterium 30 Colony Forming Unit x 10^9^ to be taken twice daily for 8 weeks.  Composition of probiotics:   \| Lactobacillus acidophilus \| 107mg \| \| --- \| --- \| \| Lactobacillus casei \| 107mg \| \| Lactobacillus lactis \| 107mg \| \| Bifidobacterium bifidum \| 107mg \| \| Bifidobacterium infantis \| 107mg \| \| Bifidobacterium longum \| 107mg \|   Placebo group will receive a 3g sachet of substance (powder form) that has no therapeutic effect to be taken twice daily for 8 weeks.  All test products will be concealed in sealed envelopes, to ensure blindedness  **10.3 STUDY ASSESSMENT**  All patients will be assessed at baseline and week 8 for improvement in constipation symptoms using the Garrigues Constipation Questionnaire^35^, Quality of Life by using self- administered PDQ39 questionnaire (malay version)^36^, disease severity by using MDS-UPDRS and non-motor symptoms by using NMS scale . The Gastrointestinal transit time will be assessed at baseline and week 8 using red carmine capsule. Compliance to treatment, side effects and clinical assessments will be performed by a blinded assessor at baseline and week 8 for both groups.  **Gastrointestinal Transit Time Protocol**  Following randomization, subjects will be instructed to ingest 4 red carmine capsule after last bowel opening. Red carmine capsule is a food colorant and non-toxic to body which is used to measure GTT. The time of ingestion will be recorded. GTT is measured from the time of red carmine capsules consumption and first appearance of red colored stool. The duration from time of ingestion and appearance of red colored stool (Gastrointestinal transit time) will be recorded by patient at baseline, and week 8. The use of laxatives is not forbidden, but patients are required to use as per needed. GTT was measured during pre and end treatment in both groups.  **Constipation-Related Symptom Assessment**  Constipation related symptoms will be assessed using the Garrigues Constipation Questionnaire (GQ)^35^ which is a 21-item that was developed to define the presence of chronic constipation. Only 13 of the 21 items are related to bowel habits. The Rome 111 criteria were used to define constipation. The items are scored using two different four-point Likert scales. The first consisted of ‘never’, ‘sometimes’ (25% of the time) and ‘always’. The second consisted of ‘never’, ‘fewer than once a week’, ‘one or more times a week’ and ‘every day’. Total and cut off scores were not reported.  **Quality Of Life Assessment**  Baseline Quality of life patients will be assess using self-administered PDQ-39^36^ Questionnaire(Malay version) and end of intervention, subject will be assessed again using the same questionnaire. PDQ-39 questionnaire contains 39 items with each item was rated by the patients using one of five categories, from 0 (never) to 4 (always). PDQ-39 summary index (PDQSI) is calculated by dividing the sum of the total raw score by the maximum possible score (156 or 152 points, depending on the patient’s marriage status) and multiplying by 100. In this study, we will use PDQSI as a standardized index for representing PD patients’ life quality.  **Non Motor symptoms (NMS) assessment**  Severity of Non Motor symptoms of each individual will be assess using NMSS Questionnaire. Frequency and severity of each NMS are taken into account. Final total score of disability (0=no disability; 360=maximal disability).  **DDisease severity assessment**  Parkinson Disease severity assessment will be assess using MDS-UPDRS questionnaire. MDS UPDRS has four parts which include nonmotor experiences of daily living (13 items), motor experiences of daily living (13 items), motor examination (18 items), and motor complications (six items). Each subscale now has 0-4 ratings, where 0 = normal, 1 = slight, 2 = mild, 3 = moderate, and 4 = severe.  10.4 **VALIDITY OF TOOLS**  NMS and MDS-UPDRS are public domain questionnaire  Validated score : PDQ 39 (malay version)- permission obtained from author  Garrigues Constipation Questionnaire- awaiting permission from author  **11. STASTICAL ANALYSIS**  Statistical Package for the Social Sciences (SPSS) Software version 2 will be used for statistical analysis. Age, height, weight, body mass index (BMI) and gender were compared between the groups by Student’s t-test and the chi-squared test. General Linear Model will be used to compare intestinal transit time in probiotics and placebo groups before and after 8 weeks of intervention. Pre- and post-probiotics consumption data on clinical evaluation of constipation that will be obtained from all the questionnaires namely Rome III criteria, PDQ-39 Questionnaire and Garrigues Constipation Questionnaire will be analysed using Mc Nemar Test. Independent t-test will be used to compare the differences of intestinal transit time in both groups. Pearson correlation and Simple linear regression analysis will be utilized to explore the relationship and effect between two numerical variables. A p-value <0.05 will be considered as statistically significant.  **11.1 SAMPLE SIZE CALCULATION**  The sample size is being calculated based formula comparing between two proportions. Sample size calculation was performed according to a study by Sakai et al^32^ based on value reported on changes in percentage of bowel movements and complete bowel movements after 3 weeks of probiotics treatment where there was a significant decreased from 73.7% to 36.8%,  Formula for sample size comparing two proportions:  [figure not shown]  Sample size was estimated as follows :  p1 = 0.737  p2 = 0.368  zα = 1.96  zβ = 0.84  n = 0.737 (1 – 0.737) + 0.368 (1 – 0.368 ) X (1.96 + 0.84) ^2^  (0.737 – 0.368) ^2^  n = 0.193831 + 0.232576 X 7.84  0.136161  n = 25 per group  The number of samples per group is further added 20% to compensate for non-response and lost to follow up. The final samples required for each group is 30 patients. |

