**Garrigues Survey – Constipation^1^**

|  |  | | | |  | |  | |  |  |  |
| --- | --- | --- | --- | --- | --- | --- | --- | --- | --- | --- | --- |
| **Q1.** Indicate your age. | | | | | | |  | | **Q11.** How often are your stools hard? | | |
|  | | | | |  | |  | |  | Never |  |
|  |  |  |  |  |  | |  | |  | Sometimes (less than 25% of time) |  |
|  |  |  |  |  |  | |  | |  | Often (more than 25% of time) |  |
|  |  |  |  |  |  | |  | |  | Always |  |
|  | | | | | | |  | |  |  |  |
| **Q2.** Indicate your gender. | | | | | | |  | | **Q12.** Do you feel a blockage in the anus that makes it difficult to pass the stool? | | |
|  | Male | | | |  | |  | |  | Never |  |
|  | Female | | | |  | |  | |  | Sometimes (less than 25% of time) |  |
|  |  | | | |  | |  | |  | Often (more than 25% of time) |  |
|  |  |  |  |  |  |  |  |  |  | Always |  |
|  |  | | | |  | |  | |  |  |  |
| **Q3.** Indicate your educational level | | | | | | |  | | **Q13.** Do you need to press around the anus or vagina to complete a bowel movement? | | |
|  | Primary | | | |  | |  | |  | Never |  |
|  | Secondary | | | |  | |  | |  | Sometimes (less than 25% of time) |  |
|  | Tertiary | | | |  | |  | |  | Often (more than 25% of time) |  |
|  | Postgraduate | | | |  | |  | |  | Always |  |
|  |  | | | |  | |  | |  |  |  |
| **Q4.** Indicate your job | | | | | | |  | | **Q14.** Do you spend more than 10 minutes on the toilet to pass the stools? | | |
|  | | | | | | |  | |  | Never |  |
|  |  |  |  |  |  |  |  | |  | Sometimes (less than 25% of time) |  |
|  |  |  |  |  |  |  |  | |  | Often (more than 25% of time) |  |
|  |  |  |  |  |  |  |  | |  | Always |  |
|  | | | | | | |  | |  |  |  |
| **Q5.** Indicate the amount of fibre in your diet | | | | | | |  | | **Q15.** How many bowel movements do you usually have each week? | | |
|  | Low (less than 3 servings per day) | | | |  | |  | |  | | |
|  | Medium (3-5 servings per day) | | | |  | |  | |  |  |  |
|  | High (more than 5 servings per day) | | | |  | |  | |  |  |  |
|  | *1 serving = ½ cup | | | |  | |  | |  |  |  |
| **Q6.**  How often do you perform physical exercise? | | | | | | |  | | **Q16.** Do you take oral laxatives? | | |
|  | | Never | | | | |  | |  | Never |  |
|  | | Sometimes (less than 3 times per week) | | | | |  | |  | Fewer than once a week |  |
|  | | Habitually (more than 3 times per week) | | | | |  | |  | One or more times a week |  |
|  | |  | | | | |  | |  | Every day |  |
|  | | | | | | |  | |  |  |  |

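### Section 10.1 puts the second transit test after the last sachet, 10.3 leaves this open, and laxative intake during the tests is neither timed in the readable record nor used in the GTT analysis

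*Combined protocol and SAP*

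**What the plan says.** Section 4.1 lists two primary objectives. One concerns constipation and the other is "To determine the effects of probiotics on Gastrointestinal Transit Time (GTT) compared to placebo".

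**Timing.** The sachets are "to be taken twice daily for 8 weeks" (Section 10.2). Section 10.1 then says: "Once consumption completed, subjects need to consume again another 4 red carmine capsule and GTT will be measured and recorded again". Section 10.3 says: "The Gastrointestinal transit time will be assessed at baseline and week 8 using red carmine capsule". Its GTT subsection adds "GTT was measured during pre and end treatment in both groups" and, for the start of the clock, "subjects will be instructed to ingest 4 red carmine capsule after last bowel opening". The clock stops at the first red stool. The flow chart in Section 12 lists GTT determination with the week-8 visit.

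**Laxatives.** Section 5.1 names lactulose as standard therapy, describes it as promoting motility, and advises its use as needed. The GTT subsection of 10.3 repeats the permission: "The use of laxatives is not forbidden, but patients are required to use as per needed".

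**Data on laxatives.** The Garrigues questionnaire, given at baseline and week 8, asks "Do you take oral laxatives" (Q16), with parallel items on suppositories (Q17) and enemas (Q18). Each has four frequency categories. The screening form also has a field for current medications.

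**Analysis.** Section 11 compares GTT with a General Linear Model and an independent t-test, and applies the McNemar test to pre/post questionnaire data.

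**The concern.** The protocol leaves two things open about what the second GTT value represents.

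First, a patient who follows 10.1 literally finishes the supply, waits for a bowel opening, swallows the capsules and then waits for red stool, all without product. The slower the transit, the longer the off-product interval. A patient who follows 10.3 might do the test during the last days of dosing. The two values answer different questions, and nothing in the readable text says which is meant or limits the gap after the last sachet.

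Second, lactulose acts, by the protocol's own description, on the quantity being measured. As-needed use follows symptoms. If the probiotic works, placebo patients may well take more laxative, which would narrow the difference between arms. With frequency categories alone, nobody could tell afterwards whether a given transit was measured with or without a laxative.

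At stake is how a small or null GTT difference can be read: as no effect, as an effect that had worn off, or as one offset by laxative use.

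**Working it through.** **1. The plan's own calculation.** Inputs from Section 11.1 are p1 = 0.737, p2 = 0.368, zα = 1.96 and zβ = 0.84.

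n = [0.737 × 0.263 + 0.368 × 0.632] × (1.96 + 0.84)² / (0.737 − 0.368)²
= (0.193831 + 0.232576) × 7.84 / 0.136161 = 24.55, rounded up to 25; 25 × 1.20 = 30 per group.

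The stated 25 and 30 reproduce. They concern a proportion, so GTT has no sample-size calculation and this point changes no printed figure.

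**2. The timing statements compared.**

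| Place | Statement in substance | On or off product? |
|---|---|---|
| 10.1 | capsules after consumption is complete | off, read literally |
| 10.3, opening paragraph | baseline and week 8 | either |
| 10.3, GTT subsection | before and at end of treatment | either |
| Section 12, flow chart | with the week-8 visit, post intervention | either; leans to off |

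Only 10.1 orders the capsules relative to the last sachet. The other statements are compatible with it and also with a test on product.

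**3. What is known about laxatives.** Q16–Q18 give frequency at both visits. They do not give the product, the amount, the date or a recall period. McNemar is a paired before/after test of a two-category outcome, so even if it were applied to a dichotomised Q16 it would not compare the arms. Section 11 names no laxative covariate for GTT.

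**4. Illustration of dilution.** The documents give no GTT effect or SD, so the effect is expressed in SD units and the share lost, f, is an assumption. Normal approximation, two-sided 5%.

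Detectable difference with 80% power at 25 per arm: (1.960 + 0.842) × √(2/25) = 0.79 SD. At 30 per arm: 2.802 × √(2/30) = 0.72 SD.

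If a share f of a 0.79 SD effect is lost, power at 25 per arm is Φ(2.802 × (1 − f) − 1.960), and the number per arm that restores 80% is 25/(1 − f)²:

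| Share lost (assumed) | Power at 25 per arm | n per arm for 80%, unrounded |
|---|---|---|
| 0% | 80% | 25.0 |
| 10% | 71% | 30.9 |
| 20% | 61% | 39.1 |
| 30% | 50% | 51.0 |
| 50% | 29% | 100.0 |

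The table shows sensitivity only. Nothing in the documents says which row applies, or that any loss occurs.

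**The case against.** The case on the other side is substantial.

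- **Laxative use is recorded.** A reader might infer that it goes uncaptured. It does not: Q16–Q18 are asked at both visits. Nor do the documents exclude these items from the planned questionnaire analysis. What stands is narrower: no time-linked record around the tests, no between-arm comparison and no laxative term for GTT.
- **The timing may not be a contradiction.** Week 8 and end of treatment fit capsules taken just as the supply runs out. That is fair: this is an ambiguity to resolve, and 10.1 is the only statement that resolves it, towards off product.
- **Fading is assumed.** No offset time is given. Exclusion criterion 5, which bars probiotics in the 2 weeks before baseline, suggests the authors expect some carry-over. So the text does not show that an off-product test loses any effect.
- **As-needed laxatives are a legitimate design choice.** They are allowed in both blinded arms and at the baseline test too. The trial can be read as probiotic versus placebo on top of usual care, and a null would then mean no demonstrated added benefit in that setting. A reader might infer that a null could not be interpreted at all; that goes too far. Greater laxative use on placebo is plausible but undocumented.
- **Part of the file is not visible.** Some pages and figures are missing, so a GTT record form with laxative fields could exist. The criticism is limited to the readable text.

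**Conclusion.** The point holds in a limited form and is worth acting on because the repair is cheap. Read literally, Section 10.1 measures the second value of a primary endpoint after the last sachet, and 10.3 does not settle the matter, so the passages must be reconciled. Laxatives are permitted during both tests. Their frequency is known, but in the readable text their intake within the test window is not, and the planned GTT analysis does not take laxative use into account.

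The same rules apply to both arms, so the main consequences are an endpoint that is not fully defined and possible dilution. It becomes a between-arm distortion only if laxative use differs by arm; more use on placebo would shrink the difference. The documents establish neither fading nor differential use, and the size cannot be derived from them. The fall from 80% to between 71% and 29% power rests on an assumed loss of 10% to 50% of an assumed 0.79 SD effect with 25 evaluable per arm.

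**What to change.** 1. **Timing.** Reconcile 10.1 with 10.3 so that the second capsules are swallowed while the assigned sachets are still being taken, near the end of the existing 8 weeks. This concerns measurement timing only. Product, duration and the laxative rule stay as they are. Record the time of the last sachet beside the capsule and red-stool times, so that any off-product interval is visible.
2. **Record.** Add laxative intake (product, amount, time) to both GTT records, from the day before capsule intake until first red stool.
3. **GTT model.** Compare week-8 GTT between arms, adjusted for baseline GTT and baseline Q16. Both are measured before the first sachet, so adjustment is safe.
4. **Reporting.** Tabulate week-8 Q16–Q18 and the test-window intake by arm as supportive information. Do not enter them as covariates in the GTT model: they arise after randomisation and may themselves reflect treatment.
5. **Interpretation.** State that the GTT comparison is made with laxatives used as the protocol allows.

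**Cost.** A reworded instruction, a few lines on a form, two baseline covariates and one table. Capsules must be handed out before the final visit, and the test falls slightly before the end of week 8. In very slow patients red stool may still appear after the last sachet; the documents give no GTT distribution from which to set a lead time, so the sponsor must choose one and state it.

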**Screening :**

**Rome III Criteria – Constipation Module**

**Negative Fecal occult blood**

**Fulfil inclusion/ exclusion criteria**

2^ND^ VISIT- WEEK 8

Constipation assessment with GQ

Quality of life assessment with PDQ39

Disease severity assessment with MD S- UPDRS

Non motor symptoms assessment with NMS

Questionnaires

Determination GTT

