**13. ETHICAL ISSUES**

There will be no ethical issues on this study as following apply:

Consent from patient who agreed to be enrolled for the study of probiotics

Patients were actively monitored for gastrointestinal disorders (common adverse events)

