| **Q7.** Indicate which drugs you are taking | | | | | | |  | | **Q17.** Do you need to use suppositories to have bowel movements? | | |
|  | | Non steroidal anti inflammatory (NSAIDs) | | | | |  | |  | Never |  |
|  | | Anxiolytics | | | | |  | |  | Fewer than once a week |  |
|  | | Calcium channel antagonist | | | | |  | |  | One or more times a week |  |
|  | | Female hormone based drugs | | | | |  | |  | Every day |  |
|  | | |  |  | |  | |  |  |  |  |
|  | | | | | | |  | |  |  |  |
| **Q8.** Have you felt constipated? | | | | | | |  | | **Q18.** Do you need to use enemas to have bowel movements? | |  |
|  | | Yes | | | | |  | |  | Never |  |
|  | | No | | | | |  | |  | Fewer than once a week |  |
|  | |  | | | | |  | |  | One or more times a week |  |
|  | |  | | | | |  | |  | Every day |  |
|  | |  | | | | |  | |  |  |  |
| **Q9.** Do you strain during a bowel movement? | | | | | | |  | | **Q19.** Have you visited a doctor because of constipation? | |  |
|  | | Never | | | | |  | |  | Yes |  |
|  | | Sometimes (less than 25% of time) | | | | |  | |  | No |  |
|  | | Often (more than 25% of time) | | | | |  | |  |  |  |
|  | | Always | | | | |  | |  | |  |
|  | |  | | | | |  | |  |  |  |
| **Q10.** Do you feel an incomplete emptying sensation after a bowel movement? | | | | | | |  | | **Q20.** Have you presented with abdominal pain more than six times this past year? | |  |
|  | | Never | | | | |  | |  | Yes |  |
|  | | Sometimes (less than 25% of time) | | | | |  | |  | No |  |
|  | | Often (more than 25% of time) | | | | |  | |  |  |  |
|  | | Always | | | | |  | |  |  |  |
|  | |  | | | | |  | |  | |  |
|  | |  | | | | |  | | **Q21.** Have you presented with loose or watery stools? | |  |
|  | |  | | | | |  | |  | Yes |  |
|  | |  | | | | |  | |  | No |  |
|  | |  | | | | |  | |  |  |  |

^1^Garrigues et al *Am J Epidemiol* 2004

PDQ-39 (MALAY)

| Name:  MRN:  (Sticker) |  | Day 0 |  |  |
| --- | --- | --- | --- | --- |
|  |  | Date | / / 2018 | |

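### The only scheduled side-effect and compliance inquiry after dosing starts is at week 8; separately, section 10.1 makes the final outcome assessment depend on finishing the product

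*Combined protocol and SAP*

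**What the plan says.** Four places in the protocol bear on this.

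- **Section 10.3, side effects and compliance:** "Compliance to treatment, side effects and clinical assessments will be performed by a blinded assessor at baseline and week 8 for both groups". No condition about completing treatment is attached.
- **Section 10.3, outcomes:** "All patients will be assessed at baseline and week 8 for improvement in constipation symptoms", followed by the quality-of-life, severity and non-motor instruments. GTT is set for the same two time points.
- **Section 10.1, outcomes:** "Final assessment will be done once subjects completed all the probiotics or placebo given(week 8", and the listed content is the baseline questionnaires. A separate sentence in 10.1 places the second carmine test after consumption is complete.
- **Section 13:** "Patients were actively monitored for gastrointestinal disorders (common adverse events". No time, method or assessor is given.

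The flow chart in section 12 goes from a week 0 visit to "2^ND^ VISIT- WEEK 8", with nothing shown between.

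**The concern.** Section 13 offers monitoring for gut disorders as part of the ethical case and names them as the common adverse events. In the visible schedule, that monitoring amounts to one retrospective inquiry at the end of dosing. A gut symptom in the first weeks that the patient does not volunteer is first asked about at week 8, from memory. The same holds for missed doses, for a decision to stop, and for the reason behind it. As-needed lactulose is allowed and can itself change bowel habit, so undated symptoms are hard to place relative to lactulose or to the study product.

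The wording of 10.1 raises a different matter. If staff follow it literally, a patient who stops early never reaches the trigger for the final questionnaires and the second GTT. Constipation and GTT are the two primary objectives, so outcome data would then be kept or lost according to whether the patient finished the product.

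**Working it through.** **1. What is scheduled after exposure starts**

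Inputs: two sachets a day for 8 weeks (10.1, 10.2); side effects and compliance at baseline and week 8 (10.3); sachets handed out after the first-visit assessments (10.1).

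- Dosing period: 8 × 7 = 56 days.
- Maximum exposure before the first on-study inquiry: 2 × 56 = 112 sachets.
- Scheduled contacts between week 0 and week 8: 0.
- Scheduled inquiries after dosing starts: 1, at week 8.

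With one call at week 4 (day 28):

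- Longest wait from first dose to first inquiry: 28 days instead of 56.
- Maximum exposure by then: 2 × 28 = 56 sachets instead of 112.
- Scheduled inquiries after dosing starts: 2 instead of 1.

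**2. Section 13 set against the schedule**

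Section 13 asserts active monitoring. The only dated side-effect assessment is the one in 10.3. The flow chart adds no contact between the two visits. The Gantt chart has a row that includes follow-up, but no contact is described there. So section 13 states an intention that the visible schedule meets only at week 8.

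**3. Early stoppers, sentence by sentence**

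- Side effects and compliance (10.3): both groups, at week 8, no completion condition. An early stopper is due this inquiry.
- Questionnaires: 10.3 says all patients at week 8; 10.1 says once the product is finished. These conflict for an early stopper.
- GTT: 10.3 says week 8; 10.1 says after consumption is complete. The same conflict arises.

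The conflict is confined to outcome follow-up.

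**4. Cost of the calls**

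The number of patients comes from section 11.1, and the plan's figure reproduces: n = (0.193831 + 0.232576) × 7.84 / 0.136161 = 24.55, rounded up to 25 per group; 25 × 1.2 = 30 per group, 60 in all. The proposed change does not alter it.

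Assumptions, not from the documents: 60 mid-treatment calls, 0 to 10 early-stop calls, 5 to 10 minutes per call, 5 minutes of data entry, and one failed attempt of 2 minutes per completed call.

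- Low: 60 × (5 + 5 + 2) = 720 min = 12.0 h.
- High: 70 × (10 + 5 + 2) = 1,190 min = 19.8 h.

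**The case against.** The strongest reply has four parts.

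- **Section 13 does plan monitoring.** This stands as far as it goes. The supportable statement is that no contact is *scheduled* during dosing, not that no monitoring is intended. A statement without a time or method still gives staff nothing to carry out.
- **The argument leans on silence in an incomplete text.** The flow chart was disordered in extraction and omits side effects and compliance even at the visits where 10.3 places them, so its silence is weak evidence. Some pages and forms are not shown, and a patient-initiated reporting route or a side-effect form may exist there. The point therefore rests mainly on 10.3 and is limited to scheduled inquiry in the visible text.
- **Early stoppers are covered for side effects.** This stands. A reader might infer from 10.1 that they are never asked. The documents do not support that: the 10.1 sentence lists questionnaires only, and the side-effect sentence in 10.3 is unconditional. Planning a compliance assessment at week 8 also suggests that incomplete takers are expected there.
- **The constipation questionnaire proves nothing about side effects.** This also stands. A reader might take the recall wording of the Garrigues items (for example "Have you presented with abdominal pain more than six times this past year") as showing that side effects cannot be dated. Those items belong to an outcome instrument. Side effects are assessed separately on a form that is not visible, which may well ask for dates.

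The proposed call also has limits. A patient who stops in week 1 and says nothing is asked about three weeks later, and an unreported stop after the call still surfaces only at week 8.

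**Conclusion.** The point holds in two separate parts.

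- **Side effects and compliance.** The visible plan schedules one inquiry after dosing starts, at the end of up to 56 days and 112 sachets, and nothing before it that would give effect to section 13. This weakens the timing and detail of tolerability and compliance data.
- **Outcome follow-up.** Sections 10.1 and 10.3 disagree on whether a patient who stops early has the week 8 questionnaires and GTT. If 10.1 were followed, those outcomes would be lost.

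A reader might go further and conclude that events are being missed in a known number, or that the efficacy comparison is biased. Neither follows. The documents give no event rates, onset times or stopping rates; the 20% allowance in 11.1 is for non-response and loss to follow-up, not for stopping the product. Section 10.3, as written, keeps all patients in the week 8 assessment. This is an inexpensive improvement worth making, not a defect that undermines the trial. It assumes that no contact schedule sits in the pages not shown.

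**What to change.** 1. Amend 10.3 and the flow chart so that the existing blinded assessor telephones each patient once mid-treatment (for example at week 4), and once if a patient is found to have stopped early. If the week 4 call itself reveals the stop, it serves as both. Ask about gut symptoms with dates, compliance, the reason for stopping, and lactulose use. Cite this schedule in section 13.
2. State in 10.1 that the week 8 questionnaires, GTT and side-effect assessment apply to all randomised patients, whether or not they completed the product.

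The second change costs a sentence, plus the effort of bringing early stoppers back at week 8. The first costs about 12 to 20 hours of staff time over the trial on the assumptions above and a minor amendment; it needs no new clinical procedure and leaves the sample size unchanged. Calls may slightly prompt reporting or compliance. This would apply in both arms with patient and caller blinded, but its size is not known.
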